#### Integrated mHealth Device: unWIRED Intervention

Participants will receive case management for their mental illness as well as wearing the Embrace2 device. This device sends physiological measurements to the Empatica Research Portal, which can then be relayed to health service computers for the treating case manager to view. A dashboard generated by the program Splunk [25] provides case managers with information regarding each participant’s arousal, sleep, and activity from the previous day. Splunk captures, indexes, and correlates real-time data and generates graphs, reports, dashboards, and visualizations. The dashboard provides a visualization of the participant’s EDA and activity over a 24-hour period, as well as representing activity through *speed meters*, which present the participant’s level of activity. The program provides password-protected weblinks allowing clinical staff to view the dashboard from their clinical site. Each participant will also have access to activity-based information, which will be transmitted to their mobile phone’s Mate App. Based on the information provided, case managers and/or participants may choose to alter their management plan. For example, periods of high arousal and/or poor sleep may indicate a need for a medication change or a more assertive intervention. Continuous data will be visually inspected for significant deviations in physiological measures and the *speed meters* will be used to alert clinicians of significant change. Physiological information relayed to both the case manager and participant will be regularly reviewed and discussed during team meetings. Where possible, the use of the dashboard will be recorded in electronic medical records. Adherence to the device will be monitored through a portal that shows if the device is being worn and the data are streaming. If there are consecutive days of nonadherence, the research psychologist (SB) will contact the participant to find out the reason for the disconnection and attempt to troubleshoot. For example, the psychologist may ask participants to remember to wear or charge the device and insure it is paired with their phone.

#### Unintegrated mHealth Device: Control Condition

Participants in the control condition will receive their standard care in addition to being given an Embrace2 to self-monitor their activity levels. This device will provide information to each participant regarding their activity; however, unlike in the integrated condition, information will not be returned to their treating case manager—the device will not be integrated with the mental health team. The device can be used at each participant’s discretion, without prompting or oversight from their case manager.

### Randomization

Randomization will be conducted by an independent statistician not associated with the study. Randomly permuted blocks of 4 participants will be centrally generated using a computer-generated algorithm. The randomization sequence will be managed by staff independent of the project who will notify the clinical researcher of the randomization allocation. Participants, case managers, and clinician researchers at any one site will not be blinded as to allocation, as those in the integrated condition will regularly discuss the intervention with their case manager.

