### Participants

The study will recruit 126 youths aged 18-25 years with a severe mental illness drawn from youth community mental health services in Western Sydney and Sydney Local Health Districts in New South Wales (NSW), Australia, where BK, JS, and AH are senior psychiatrists. Admission to these services is determined by participants experiencing moderate to severe mental illness that impairs functioning. All participants at these sites will be receiving case management for their mental illness, including regular medication monitoring and/or psychosocial treatments consistent with Australian and New Zealand College of Psychiatry guidelines. Participants will not be paid; however, they can be reimbursed for costs associated with participation, such as travel expenses or mobile phone credit.

Inclusion criteria are (1) being a current community mental health service patient, (2) aged 18-25 years, (3) having a confirmed diagnosis of serious mental illness, including schizophrenia spectrum disorders, bipolar affective disorder, severe major depressive disorder, anxiety disorder, and/or personality disorder, and (4) having the capacity to consent to the study.

Exclusion criteria are (1) being non-English speaking, (2) having greater than mild developmental disability, and (3) having an inability to comply with either the requirements of informed consent or the treatment protocol.

Substance use will not be an exclusion criterion, as the effects of stress due to substance withdrawal and self-medication are important factors in relapse. It is also important to keep the study population ecologically similar to the clinical population.

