##### The Clinical Global Impression Scale

The primary measures are consensus scores on the CGI severity and treatment response scales. Assessments are made by blinded clinicians, taking into account all relevant information to make ratings on two 7-point scales. The CGI is a brief, valid measure of symptom severity and treatment response, which has shown utility in measuring mental state as compared to similar scales [27,28].

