#### Recruitment

Recruitment will primarily be managed by the research psychologist, who will explain and provide information to case managers and service managers at the clinical sites. Case managers will ask potential participants if they are interested in being involved. If they indicate interest, the research psychologist will contact them and answer any questions they may have regarding the project.

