#### Consent, Randomization, and Initial Assessment

If a participant indicates interest in being involved, the research psychologist will ask for their written consent. Randomization will be determined by an external party who will communicate treatment condition to research staff. After consent and randomization, participants will be asked to complete a series of self-report questionnaires (see the Participant Self-Report, With Time Point, section). The psychologist will ask all participants to download the Empatica Mate App onto their phone and they will set up an Empatica account using a QR (Quick Response) code from the research portal. The Embrace2 device will be paired with the participant’s phone using Bluetooth. They will give the participant some basic instructions on how to operate the device, including how to charge it and keep it connected.

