### Power Calculations and Statistical Analysis

The primary outcome for this study is to compare changes in treatment-related outcomes before and after the intervention for participants enrolled in the integrated versus unintegrated conditions. There are currently no trials examining the augmentation of treatment with an mHealth device, so sample size estimations are made using general calculations. Assuming a moderately sized advantage of the integrated (ie, unWIRED) versus unintegrated device on outcomes (effect size=0.5, 80% power, and a 2-tailed α of .05), we will require 63 participants per group.

The RCT component generally compares measures of mental health, distress, and functioning between the conditions, adjusted for baseline scores. For example, this analysis may focus on an intent to treat using a hierarchical linear model (HLM) to test the differential effects of the two treatment conditions, because this method allows the number of observations to vary between participants and handles missing data by calculating estimates of trajectories using maximum likelihood estimation. Fixed effects could be tested for intervention condition and time of assessment. Random effects in the unstructured models provide an index of the relative effects of the treatments over time. Fixed effects parameters may be tested with the Wald test (*t* test, *P*<.05, 2-sided) and 95% confidence intervals. Analyses will focus on the primary outcomes (ie, CGI scores) and secondary outcomes (eg, APQ6, BASIS-24, DASS-21, PSQI, and AQoL-8D) between the unWIRED group and the active control group, with the main outcome points being at the 6-month follow-up relative to baseline. All results are based on estimated mean values derived from HLM analyses. The within-subjects analysis will be comprised of linear fixed effects models using physiological measurements (ie, sleep, activity, and EDA) to predict measures of mental health, distress, and functioning. Baseline variables may be used as covariates when analyzing individual and between-group differences (eg, age, illness severity, treatments, and personality differences). Thematic analysis [38] will be used to examine individual and group qualitative feedback regarding the acceptability of the mHealth device and the unWIRED intervention for participants and case managers; there will be approximately 10-20 participants in the patient and clinician groups.

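### A fixed, published block size of 4 with open allocation lets a recruiter who knows the earlier arms deduce about a third of allocations; baseline questionnaires also follow randomization

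*Protocol article*

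**What the plan says.** - **Block size.** The Randomization section fixes one size and publishes it: "Randomly permuted blocks of 4 participants will be centrally generated using a computer-generated algorithm".
- **Custody of the list.** The same section has an independent statistician produce the sequence. Staff outside the project hold it and tell the clinical researcher each result. The section on consent, randomization and initial assessment says: "Randomization will be determined by an external party who will communicate treatment condition to research staff".
- **Blinding.** "Participants, case managers, and clinician researchers at any one site will not be blinded as to allocation".
- **Who recruits.** Case managers make the first approach. After that, "Recruitment will primarily be managed by the research psychologist", and the same person asks for written consent and sets up the device (sections Recruitment and Consent, Randomization, and Initial Assessment).
- **Duties that depend on the arm.** The psychologist follows up non-adherence in unWIRED participants and may send them stress prompts by text. These prompts are for the integrated arm only (sections on the unWIRED intervention, Ecological Momentary Assessment and Trial Administration).
- **Timing of baseline.** The consent section places the initial self-report questionnaires after both consent and randomization. The statistical section adjusts the comparison between conditions for baseline scores.

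**The concern.** Holding the list centrally hides the list. It does not hide an allocation that follows from the earlier ones. In a 2+2 block whose size is public, anyone who knows the earlier arms knows the fourth allocation, and also the third when the first two match.

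If the person who follows up interest and takes consent has that knowledge, the timing or vigour of an approach can depend, even unintentionally, on the arm that comes next. A more engaged or less unwell patient could then be more likely to enter one arm. Randomization would no longer guarantee comparable groups, and covariate adjustment repairs only what was measured. Engagement matters especially here, because the intervention works through wearing the device and discussing its data.

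The order of the first visit adds a second route. If a participant or the staff member present already knows the arm when the questionnaires are filled in, the baseline self-reports can be coloured by it, and those scores are then used for adjustment.

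**Working it through.** **Inputs.** Block size 4 (Randomization). Total of 126: "The study will recruit 126 youths aged 18-25 years with a severe mental illness" (Participants). Equal groups: "we will require 63 participants per group" (Power Calculations and Statistical Analysis), which implies two of each arm per block. The article gives no figure for predictability.

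**Step 1: the plan's own figure.** With "effect size=0.5, 80% power, and a 2-tailed α of .05", reading the effect as a standardised difference:

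n per group = 2(1.960 + 0.842)² / 0.5² = 2 × 7.85 / 0.25 = 62.8, rounded up to 63.

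The stated 63 per group reproduces under the normal approximation. Nothing below alters it.

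**Step 2: allocations that are certain in advance.** There are six arrangements of a 2+2 block:

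| Arrangement | Positions known beforehand |
|---|---|
| AABB, BBAA | 3rd and 4th |
| ABAB, ABBA, BAAB, BABA | 4th only |

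Total: 2 × 2 + 4 × 1 = 8 of 24 positions = 33.3%, or 4/3 per block. Since 126 = 31 × 4 + 2, and the first two positions of a block are never certain, the expected number is 31 × 4/3 = 41.3, or 32.8% of 126.

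**Step 3: best guess.** The chance of guessing correctly at positions 1 to 4 is 1/2, 2/3, 2/3 and 1. The sum is 2.833, and 2.833/4 = 70.8%. Over 126: (31 × 2.833 + 1/2 + 2/3)/126 = 89.0/126 = 70.6%, against 50% by chance.

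Steps 2 and 3 assume an observer who knows every earlier allocation in the list and where each block starts.

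**Step 4: an observer who sees part of a common list.** Suppose a case manager sees a share f of the entries and even knows the block boundaries. Position 3 is certain if the first two match (1/3) and both were seen (f²). Position 4 is certain if both members of the earlier matching pair were seen (f²). The share certain is (f²/3 + f²)/4 = f²/3. The article does not give f, so it is an assumption:

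| f | Certain |
|---|---|
| 1/4 | 2.1% |
| 1/2 | 8.3% |
| 3/4 | 18.8% |
| 1 | 33.3% |

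**Step 5: alternatives.** Fixed sizes were enumerated exactly. Mixed sizes were simulated (1,500 trials of 126) for an observer who knows all past allocations and the possible sizes, but not their order.

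| Blocks | Certain | Best guess right |
|---|---|---|
| Fixed 4 | 33.3% | 70.8% |
| Fixed 6 | 25.0% | 68.3% |
| Fixed 8 | 20.0% | 66.6% |
| 4 and 6 at random | 5.6% | 69.2% |
| 2, 4 and 6 at random | 4.1% | 70.2% |

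Varying the size removes most of the certainty and little of the guessing.

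**The case against.** The plan has real safeguards. The list is generated and held independently, consent precedes allocation, and the primary outcome is rated blind: "Assessments are made by blinded clinicians, taking into account all relevant information to make ratings on two 7-point scales". Comparisons are adjusted for baseline scores, and illness severity is a possible covariate. Case managers, not the psychologist, choose whom to approach first, so knowledge and discretion are partly separated. All of this stands and limits the risk. It does not remove it. Blinded rating guards against biased scoring, not biased entry. Consent before allocation does not help if the next arm can be deduced before the patient is contacted. The psychologist still influences follow-up and timing.

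Some stronger readings are tempting, and the documents do not support them:

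- **That the article says one person recruits and learns every allocation.** Recruitment is only primarily the psychologist's, and those notified are called the clinical researcher or research staff. The arm-specific duties make the knowledge a strong inference, no more.
- **That one third applies to case managers.** On a common list they see only part of the sequence (Step 4). It would apply to them only if each saw a complete list, for example one for the site.
- **That sites are unbalanced.** The article neither states nor excludes stratification by site, and a condensed article may leave this to the full protocol.
- **That bias is shown.** Predictability is an opportunity. The documents give no basis for sizing an effect on the CGI.

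It is also fair to object that varying blocks leaves best-guess accuracy almost unchanged. That is true, and the gain should be described as a loss of certainty only.

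**Conclusion.** The point holds as an avoidable weakness in design, not as a contradiction or a wrong figure. For an observer who knows all earlier allocations, about 41 of 126 allocations (one third) are certain before enrolment, and the best guess is right about 71% of the time. This rests on 1:1 blocks of 4, as stated and implied, and on the inference that the research psychologist can follow the sequence. For that person the proportion is the same with one list or with a list per site, apart from incomplete last blocks.

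The baseline point is narrower. It concerns self-report questionnaires, which supply secondary outcomes. It depends on whether the arm is known by the time they are completed, which the article leaves open. The article does not place the baseline CGI relative to randomization, so nothing is claimed about it.

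**What to change.** Before enrolment, have the independent statistician regenerate the list with block sizes that vary at random, for example 4 and 6. Keep the sizes from trial staff and out of public documents; the article need say only that permuted blocks of varying, undisclosed size are used. Release each allocation only once consent and all baseline measures are recorded, and reorder the section on consent, randomization and initial assessment to match.

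Certain predictions fall from about 33% to about 4–6%, and lower if the sizes really are unknown. Best-guess accuracy stays near 70%, so recruitment should still be run without regard to earlier allocations.

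The cost is one new list, a sentence or two of text, and a small change in the order of the first visit. With blocks of up to 6, the largest possible difference between arms when enrolment stops mid-block rises from 2 to 3 participants per list (half the largest block). Sample size and power are unaffected. When the text is revised, the sponsor could also state whether site is a stratum; this is a request for clarity, not a correction.

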### Measurements

#### Overview

The primary outcome for the RCT is the extent to which the integrated mHealth device can prevent mental deterioration. The within-subjects components of the trial will examine if differences in activity, sleep, and EDA predict mental deterioration versus stability. A variety of measurements will be taken, including self-report, case manager report, biometric measures from the Embrace2, EMAs of stress, chart reviews, as well as qualitative reports from case managers and participants regarding the acceptability of the device. Multimedia Appendix 1 shows a summary of the measurements taken at each time point.

#### Assessments of Mental Deterioration

Case managers and blinded clinical staff will make monthly assessments of participants using the Clinical Global Impression Scale (CGI) [26], the Social and Occupational Functioning Assessment Scale (SOFAS) [6], and chart reviews.

##### The Clinical Global Impression Scale

The primary measures are consensus scores on the CGI severity and treatment response scales. Assessments are made by blinded clinicians, taking into account all relevant information to make ratings on two 7-point scales. The CGI is a brief, valid measure of symptom severity and treatment response, which has shown utility in measuring mental state as compared to similar scales [27,28].

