**Methods:**

This study examines whether physiological information from an mHealth device prevents mental deterioration when shared with the participant and clinical team versus with the participant alone. A randomized controlled trial (RCT) will allocate 126 young adults from community mental health services for 6 months to standard case management combined with an integrated mHealth device (ie, physiological information is viewed by both participant and case manager: unWIRED intervention) or an unintegrated mHealth device (ie, participant alone self-monitors: control). Participants will wear the Empatica Embrace2 device, which continuously records electrodermal activity and actigraphy (ie, rest and activity). The study also examines whether the Embrace2 can detect periods of mental health versus deterioration. A variety of measurements will be taken, including physiological data from the Embrace2; participant and case manager self-report regarding symptoms, functioning, and quality of life; chart reviews; and ecological momentary assessments of stress in real time. Changes in each participant’s Clinical Global Impression Scale scores will be assessed by blinded raters as the primary outcome. In addition, participants and case managers will provide qualitative data regarding their experience with the integrated mHealth device, which will be thematically analyzed.

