## Discussion

This study will determine whether integrating an mHealth device into clinical care is useful and effective in managing severe mental illness in young adults in the community. We plan to test this approach in a frontline community mental health setting, where we can examine its feasibility, acceptability, and efficacy for patients and case managers. While previous studies use mHealth devices for participants to self-monitor, this is among the first to stream information to both a patient and the treating mental health team. We hypothesize that the device will identify periods of increased stress and risk of mental deterioration.

A strength of this design is that it examines both between- and within-subjects components. An RCT is a gold standard in determining treatment efficacy, and the within-subjects design can control for individual differences. This study also takes several types of measurements regarding evidence of mental deterioration, symptoms, and functioning. Potential limitations with this protocol should also be noted. This study intends on using participants with a variety of diagnoses, with varying severities, and with psychosocial difficulties. While this increases its ecological validity, the variation may make it more difficult to detect group differences. This limitation highlights the importance of controlling for relevant variables as well as studying within-subjects variation. Furthermore, even severely unwell patients are more often stable than deteriorating, providing fewer opportunities to test the efficacy of the unWIRED approach. Hence, examining process variables is important, as is the mixed methods approach employed in this study. Finally, the design incorporates several measures to detect an effect; however, this increases the likelihood of type I error.

While ambitious, this project’s clinical implications are potentially significant. Any treatment that improves collaboration and early intervention may have a far-reaching impact on the treatment of severe mental illness in the community. The intervention could allow clinicians to remotely and unobtrusively monitor severely unwell patients in the community and provide an effective means to augment treatment.

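### Two CGI scales are named as primary, but the sample size covers one unnamed endpoint at .05, and change from baseline has no evident meaning for the treatment response scale

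*Protocol article*

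**What the plan says.** The section The Clinical Global Impression Scale names two measures: "The primary measures are consensus scores on the CGI severity and treatment response scales". Blinded clinicians score them "taking into account all relevant information to make ratings on two 7-point scales".

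Other sections describe the primary outcome differently:

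- Abstract, Methods (singular, as change): "Changes in each participant’s Clinical Global Impression Scale scores will be assessed by blinded raters as the primary outcome".
- Measurements, Overview (singular, as a concept): "The primary outcome for the RCT is the extent to which the integrated mHealth device can prevent mental deterioration".
- Power Calculations and Statistical Analysis (singular, general): "The primary outcome for this study is to compare changes in treatment-related outcomes before and after the intervention".
- The same section (plural): "Analyses will focus on the primary outcomes (ie, CGI scores) and secondary outcomes", "with the main outcome points being at the 6-month follow-up relative to baseline".

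The sample size in that section uses one effect size of 0.5, 80% power and one two-tailed alpha of .05, and arrives at 63 per group. It does not say which scale this is for. Model parameters may be tested at a two-sided .05, and comparisons are generally adjusted for baseline. On multiplicity, the Discussion grants that "the design incorporates several measures to detect an effect; however, this increases the likelihood of type I error". The article describes no control for it.

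**The concern.** A trial sized for one test at .05 has declared two primary measures. Whether success on one scale is enough, or both are needed, decides whether the cost falls on type I error or on power. While this is open, the scale that carries the main claim could be chosen after the results are known.

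The second difficulty is the fit between the analysis and one of the two scales. Severity can be rated at entry and again at 6 months, so a change is well defined. A rating of how a participant has responded to the trial condition has no natural value before that condition starts, and the article does not give the reference point of the rating. The main contrast relative to baseline is therefore clear for one primary measure and unclear for the other.

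Third, the Overview speaks of preventing deterioration and the abstract's conclusions speak of preventing relapse, while the main contrast is a CGI comparison at 6 months.

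**Working it through.** **Inputs.** Effect size d = 0.5, 80% power, two-tailed alpha .05 and 63 per group (126 in total), all from Power Calculations and Statistical Analysis. Two primary scales, from The Clinical Global Impression Scale. The correlation between the two test statistics is not given, so it is assumed and varied from 0 to 0.9. For the power figures, d = 0.5 is assumed on both scales.

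**1. The plan's own figure.** n per group = 2(z₀.₉₇₅ + z₀.₈₀)²/d² = 2(1.960 + 0.842)²/0.25 = 62.8, so 63. This matches. Power at 63: the expected test statistic is 0.5/√(2/63) = 2.806, and Φ(2.806 − 1.960) = 80.1% (79.5% with the t distribution). The figure is right for one endpoint at an undivided .05.

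**2. Either scale suffices, each at .05.** With independence, the chance of at least one false positive is 1 − 0.95² = 9.75%. For correlated statistics it is 1 − P(|Z₁| < 1.96 and |Z₂| < 1.96) under a bivariate normal.

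**3. Both scales required, each at .05.** Type I error is controlled. With independence, joint power is 0.8013² = 64.2%. Otherwise it is P(Z₁ < 0.846 and Z₂ < 0.846).

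| Assumed correlation | Family-wise error, either suffices | Joint power, both required |
|---|---|---|
| 0 | 9.75% | 64.2% |
| 0.3 | 9.5% | 66.8% |
| 0.5 | 9.1% | 68.9% |
| 0.7 | 8.4% | 71.5% |
| 0.8 | 7.8% | 73.1% |
| 0.9 | 7.0% | 75.1% |

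**4. Alpha split to .025 each.** The critical value becomes 2.241. Power on a given scale at 63 per group is Φ(2.806 − 2.241) = 71.4% (t: 70.4%). For 80% per scale, n = 2(2.241 + 0.842)²/0.25 = 76.04, so 77 per group (154 in total; t: 78 per group). If the effect is 0.5 on both scales, the chance that at least one succeeds is higher: 1 − (1 − 0.714)² = 91.8% with independence, and 77.5% at correlation 0.9 from the same bivariate normal. That is a different quantity from the one the article powered, and it does not say which scale would carry the claim.

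**5. One scale named as primary.** Step 1 applies unchanged: 63 per group, 80% power, 5% error.

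**6. Baseline.** The abstract defines the outcome as change, and the analysis section sets 6 months against baseline. The article gives neither the anchors of the response scale nor its rating at entry. The time-point table is in Multimedia Appendix 1, which is not at hand.

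**The case against.** The strongest reply is that a success rule or alpha split is commonly left to an analysis plan, which is not shown, and that the article's wording is hedged (tests may be done, the analysis may focus). That stands as far as it goes: the absence of a rule is not in itself the point. What the article does fix is two primary measures beside a calculation for one.

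Three stronger readings are tempting, and the documents do not support them.

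- **That type I error is simply inflated to nearly 10%.** The article nowhere says that either scale suffices. If both are required, the cost is power. The same raters score both scales from the same information, so independence is the least plausible assumption.
- **That the response scale can have no baseline, so the planned analysis is impossible.** The anchors and schedule are not shown. Participants are already patients of the service at entry (Participants), so response to usual care could be rated then, although that measures something other than response to the trial condition. Adjustment for baseline can also be met by adjusting for baseline CGI severity. Only the wording about change relative to baseline lacks a clear meaning.
- **That a relapse which resolves before month 6 leaves no trace.** CGI is rated monthly (Assessments of Mental Deterioration), those ratings can enter the hierarchical model, and charts are searched for hospitalizations and signs of relapse (Chart Reviews). The supportable statement is narrower: the 6-month contrast is not a relapse endpoint.

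The Overview's reference to deterioration can also be read as a concept that the CGI section then makes operational.

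**Conclusion.** The point holds in this form. The article names two primary measures and supports them with a sample size that is correct for one. The size of the problem depends on the unstated rule:

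- Either scale suffices: overall error of about 7.0% to 9.75%.
- Both required: joint power of about 64% to 75%.
- Split alpha: about 70% to 71% power on a given scale.

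These ranges rest on assumed correlations of 0 to 0.9, on d = 0.5 for both scales, on 63 analysed per group and on a two-group comparison of means as in the article's own calculation. The stated 80% power at 5% error, for a claim on an identified outcome, is kept only when one scale is named.

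On the response scale the conclusion is limited: change from its own baseline is undefined as the article stands, and the reference point needs stating. On deterioration, a 6-month CGI difference would not by itself support a conclusion that relapse was prevented.

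**What to change.** Name one primary outcome and use the same words in the Abstract (Methods), the Measurements Overview, The Clinical Global Impression Scale, and Power Calculations and Statistical Analysis. For example: blinded CGI severity at 6 months, adjusted for baseline CGI severity, tested at two-sided .05. The 63 per group then stands.

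Make CGI treatment response a secondary outcome, state its reference point, and analyse it with adjustment for baseline CGI severity rather than as change from its own baseline.

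Word the main conclusion as a difference in CGI severity at 6 months. Speak of preventing relapse only if the relapse and hospitalization data already planned under Chart Reviews support it.

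If the sponsor prefers to keep both scales as primary, the either/both rule must be stated and the sample size recalculated for it. For split alpha at 80% power per scale, that is 77 per group (154 in total).

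Naming one scale costs a change of wording and needs no further data or participants. The downside is that the response scale loses primary status.
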